## Abstract

**Background:**

Mental and neurological disorders cause a large proportion of morbidity burden and require adequate health care structures. However, deficits in the German health care system like long waiting times for access to specialized care and a lack of coordination between health care providers lead to suboptimal quality of care and elevated health care costs.

**Objective:**

To overcome these deficits, we implement and evaluate a unique stepped and coordinated model of care (the Neurologisch-psychiatrische und psychotherapeutische Versorgung [NPPV] program) for patients with mental and neurological diseases.

**Methods:**

Patients included in the program receive an appropriate treatment according to medical needs in a multiprofessional network of ambulatory health care providers. The therapy is coordinated by a managing physician and complemented by additional therapy modules, such as group therapy, internet-based cognitive behavioral therapy, and a case management. Statutory health insurance (SHI) routine data and data from a longitudinal patient survey will be used to compare the program with regular care and evaluate SHI expenditures and patient-related outcomes. A health care provider survey will evaluate the quality of structure and processes and provider satisfaction. Finally, an analysis of ambulatory claims data and drug prescription data will be used to evaluate if health care providers follow a needs-led approach in therapy. Ethics approval for this trial was obtained from the ethics committee of the chamber of physicians in North Rhine (September 13, 2017, reference No. 2017287).

**Results:**

Patient enrollment of NPPV ended in September 2021. Data analysis has been completed in 2022. The results of this study will be disseminated through scientific publications, academic conferences, and a publicly available report to the German Federal Joint Committee, which is expected to be available in the first half of 2023.

**Conclusions:**

The NPPV program is the first intervention to implement a stepped model of care for both mental and neurological diseases in Germany. The analysis of several data sources and a large sample size (more than 14,000 patients) enable a comprehensive evaluation of the NPPV program.

**Trial Registration:**

German Clinical Trials Register DRKS00022754; https://tinyurl.com/3mx9pz5z.

**International Registered Report Identifier (IRRID):**

DERR1-10.2196/37569

## Introduction

Mental and neurological diseases continue to be a challenge for health systems worldwide. When measuring disability-adjusted life years, these diseases make up the largest share of all cause morbidity burden in the European Union [1]. Chronic mental and neurological diseases often lead to a loss of quality of life, disability, and even premature death and go along with significant direct and indirect costs of illness [2-4].

From 1990 to 2017, the 27 countries of the European Union and the United Kingdom showed an increase in prevalence of stroke (+25%), dementia (+62%), Parkinson disease (+72%), and multiple sclerosis (+41%), mainly due to demographic changes in an aging population [2]. According to the models by Brinks and Landwehr [5], the number of persons with dementia might increase 2-3 times by the year 2050. For Germany, Steffen et al [6] found an increase of 26% for depression between 2009 and 2017, especially for men and younger patients. Disease prevalence for depression with mild symptoms is on average higher in Germany as compared to other European countries [7].

The increasing burden of mental and neurological diseases will require robust health care structures in the near future to secure adequate treatment for these patients. However, several deficits in the German health care system prevent patients from getting the best possible care. First, timely access to specialized neuropsychiatric care is challenging for patients with mental and neurological diseases, mostly due to a lack of sufficient outpatient care facilities for neurology, psychiatry, and psychotherapy. Almost 3 quarters of patients with a mental disease in outpatient care are treated exclusively by their general practitioners and not by psychiatrists [8], and around 8.5% of patients fail to get an initial examination from a psychotherapist within 3 months [9]. Less than 55% of all patients with newly diagnosed multiple sclerosis receive specialized care by a neurologist within 6 weeks (dementia: less than 26%) [10]. Second, allocation of care occurs without adequate prioritization. According to Walendzik et al [11], half of the psychotherapists offer an appointment to the next inquiring patient without considering clinical needs. Third, treatments do not always follow medical guidelines. Even when excluding mild cases, about 50% of patients with depression do not receive the recommended standard of care at all or an adequate treatment with antidepressants or psychotherapy [12]. Fourth, the Advisory Council on the Assessment of Developments in the Health Care System in Germany criticized a lack of coordination and cooperation between health care sectors and professionals in the treatment of mental diseases and pointed out the need for a primary professional who coordinates the treatment of patients along clinical pathways [13].

To overcome these deficits and improve treatment of people with mental and neurological diseases, we developed a stepped and coordinated care program called “neurological-psychiatric and psychotherapeutic care” (Neurologisch-psychiatrische und psychotherapeutische Versorgung [NPPV]) for patients in the region of North Rhine, Germany. We hypothesize that our model of care will reduce direct and indirect costs of illness, improve quality of care and adherence with medical guidelines, enable a low-threshold access to care and increase health-related quality of life in patients as well as satisfaction with health care situation of patients and health care providers.

## Methods

### Intervention: The NPPV Program

The NPPV program is a stepped and coordinated model of care for mental and neurological diseases. The program aims at increasing efficiency of care, improve patients’ health outcomes, and reduce direct and indirect health costs. Each patient in the program receives an early evaluation of the patients’ needs for care followed by a timely and appropriate treatment in a multiprofessional network of outpatient health care providers. The network includes specialists from neurology and psychiatry as well as psychotherapists. To plan, coordinate, and ensure an individual treatment according to medical guidelines, every patient is assigned to a managing physician or therapist. These physicians/therapists are the primary contacts for the patients and guide the patient within the network and health care system in general. They also provide special consultation hours, cooperate with other health care professionals in the network and self-help organizations, and may choose from a wide range of additional therapy modules in the program. These modules include group therapy, internet-based cognitive behavioral therapy (ICBT), and an outpatient case management for patients carried out by the NPPV coordination office.

Group therapies are of particular importance for the treatment of mental and neurological diseases and are part of national medical guidelines for depression, posttraumatic stress disorder, or other severe mental diseases [14-16]. In the NPPV program, group therapies may be offered by all qualified health care providers in the network. Possible types of group therapy include (but are not limited to) psychoeducation, neuroeducation and training, strengthening of personal resources, and family counseling. These therapies are supported by the NPPV coordination office, for example, with regard to making appointments.

ICBT may be applied as an alternative or in addition to psychotherapeutic and psychiatric care. These therapies are low-threshold psychosocial interventions and are effective in reducing symptoms, especially for depression, anxiety disorders, panic disorders, and social phobia, and are highly accepted by patients [17-19]. In NPPV, we integrated the digital mental health program called Novego, which has been found to be effective in the reduction of anxiety and depressive symptoms in general and in patients with schizophrenia [20-22]. Novego offers 3 different courses with a focus on depression, burnout, or anxiety. The managing physician or psychotherapist can generate an access code to these courses for a patient. With these codes, patients are able to follow the courses on the internet in their own pace. The administrative tasks related to the courses are carried out by the NPPV coordination office.

Beside the central coordination office, health care providers in the NPPV network are supported by regional network managers. Tasks of the network managers are recruitment of new network members, implementation of trainings for the professionals, organization of regular quality circles, administrative support for professionals, and quality management. Additionally, physicians and psychotherapists are connected with a common web-based infrastructure (“IVPnet”) for patient administration, treatment management, and communication.

The program is funded by the Innovation Fund (“Innovationsfonds”), which was established to support innovative health care projects in Germany in 2015, and financed by the statutory health insurance (SHI) system.

### Study Design and Research Questions

The NPPV study is a prospective cohort study with a pragmatic design [23]. Beside the intervention group (participating patients), 2 control groups are drawn by matching techniques. Patients in the intervention group have immediate access to a stepped, coordinated, and comprehensive care program according to medical needs, whereas patients in the control groups receive regular care. In addition, health care providers are participating in a longitudinal survey.

We aim to answer the following research questions: first, does the intervention reduce SHI expenditures per patient? Second, are patients in the intervention group more satisfied with their treatment and do they show a higher quality of life than patients in the control group? Third, can the NPPV structures and processes be established as intended and do they lead to a higher satisfaction among health care providers? Fourth, can the NPPV program induce a more unmet-needs–based approach in the treatment of mental and neurological diseases (eg, do physicians and therapists focus on patient with a higher demand for care and do they follow medical guidelines more closely)?

### Study Population and Recruitment

We plan to recruit up to 14,000 patients for the intervention group in the region of North Rhine, Germany. The enrollment period begins in December 2017 and ends in June 2021. Patients eligible for participation in the NPPV program will be identified by their regular outpatient or inpatient health care providers or by their nursing home. They will be referred to a physician or therapist within the NPPV network, who does an entry examination to check eligibility. Inclusion criteria are as follows: age≥18 years, insurance in one of the participating health insurance companies (“AOK Rheinland/Hamburg,” “Continentale BKK,” and “BKK Deutsche Bank”), and 1 or more medical condition of 7 indication groups as outlined in Table 1. Participation in the NPPV program is voluntary. All patients need to give written informed consent to participate in the program and accompanied study.

**Table 1 table1:** Medical inclusion and exclusion criteria for indication groups.

Indication group	ICD-10-GM-Codes^a^	Additional criteria
Affective disorders (including anxiety and depression, excluding mania and bipolar disorder)	F30-F39, F41.2	Inclusion when more than 3 weeks unable to work OR at least 2 hospitalizations in 2 years OR minimum score in Mini-ICF Rating for mental disorders
Psychosis (including mania and bipolar disorder)	F20- F31	Inclusion of all patients
Posttraumatic stress or adjustment disorder	F43	Inclusion of all patients
Dementia	F00, F01, G30	Inclusion of all patients
Multiple sclerosis	G35	Inclusion of all patients
Parkinson disease	G20-G22	Inclusion of all patients except vascular parkinsonism (G21.4)
Stroke	I63-I64	Inclusion of all patients with dysfunctions or disabilities, for example, spasticity or cognitive impairment

^a^ICD-10-GM: International Statistical Classification of Diseases and Related Health Problems.

### Study Outcomes and Data Sources

#### Overview

The primary study outcome is the overall SHI expenditures per patient in 12 months after inclusion. Secondary outcomes include SHI expenditures for psychiatric and neurological treatments, hospitalizations (frequency and length of stay), patient-related outcomes (ie, health-related quality of life, satisfaction with health care, and use of intervention modules), and provider-related outcomes (ie, satisfaction, structure and process quality, and needs-led approach).

Data to evaluate the outcomes stem from SHI routine data, outpatient claims data, drug prescription data, a patient survey, and a provider survey. All outcomes and the corresponding data sources are summarized in Table 2.

**Table 2 table2:** Study outcomes and data sources.

Outcomes			Data source
**Primary outcome**			
	SHI^a^ expenditures per patient over 12 months	SHI routine data	
**Secondary outcomes**			
	1. SHI expenditures for psychiatric and neurological treatments per patient over 12 months	SHI routine data	
	2. Frequency of hospitalizations and length of stay over 12 months	SHI routine data	
	3. Frequency of hospitalizations with ICD^b^ codes from inclusion criteria and length of stay over 12 months	SHI routine data	
	4. Discontinuation of medical treatment over 12 months	SHI routine data	
	5. Number of days with incapacity for work over 12 months	SHI routine data	
	6. Health-related quality of life	Patient survey	
	7. Satisfaction with provided health care	Patient survey	
	8. Utilization of intervention modules	Patient survey	
	9. Health care provider satisfaction	Provider survey	
	10. Structure and process quality	Provider survey	
	11. Needs-led approach at health care provider level	Ambulatory claims data and drug prescription data	

^a^SHI: statutory health insurance.

^b^ICD: International Statistical Classification of Diseases and Related Health Problems.

#### SHI Routine Data

The participating health insurance companies (“AOK Rheinland/Hamburg,” “Continentale BKK,” and “BKK Deutsche Bank”) provide claims data on inpatient treatment, outpatient treatment, rehabilitation, drug prescriptions, and incapacity to work as well as basic personal information (eg, age, gender, and insurance periods) for participants as well as for 2 pools of control patients. Selection criteria for the first pool of control patients are ICD code of inclusion diagnosis (see Table 2; secured diagnosis of an outpatient health care provider that participates in the NPPV program), age≥18 years at time of diagnosis, and no participation in other special treatment contracts regarding the inclusion diagnoses (this is a pool to generate propensity scores for matching). The second pool consists of patients with the same selection criteria as the first pool, except that these patients should not be treated by a health care provider that is participating in the NPPV program (this is the pool to draw the control group via propensity score matching).

Data are provided at the end of the study and will include data from 4 quarters before inclusion date until March 2021 on each participant that started participation at least in March 2020 and control patients. Inclusion dates for potential control patients are determined by date of inclusion diagnosis. The permission to use the routine data of the participating insurance companies was granted by the State Ministry of Employment, Health and Social Affairs in North Rhine Westphalia.

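### The only stated source for the primary cost outcome has no identifiable place for several SHI-financed NPPV program costs, and any part left uncounted favours the intervention

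*Protocol article*

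**What the plan says.** The first research question (Study Design and Research Questions) is: "does the intervention reduce SHI expenditures per patient". Under Study Outcomes and Data Sources, the Overview states: "The primary study outcome is the overall SHI expenditures per patient in 12 months after inclusion". Table 2 gives SHI routine data as the only source for this outcome. The SHI Routine Data section then describes the delivery: the insurers "provide claims data on inpatient treatment, outpatient treatment, rehabilitation, drug prescriptions, and incapacity to work", together with basic personal information.

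The section Intervention: The NPPV Program describes what participants receive beyond regular care. On the therapy modules it says: "These modules include group therapy, internet-based cognitive behavioral therapy (ICBT), and an outpatient case management for patients carried out by the NPPV coordination office". On support for providers: "Beside the central coordination office, health care providers in the NPPV network are supported by regional network managers". The same section names a shared web platform (IVPnet) and internet courses that the managing physician or psychotherapist opens with an access code. On money it says "The program is funded by the Innovation Fund" and, later in the same sentence, "financed by the statutory health insurance (SHI) system".

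Analyses in SHI Routine Data compares participants with propensity-matched controls by regression. It does not mention adding program costs.

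**The concern.** The question is about SHI spending, and by the article's own account the program is SHI-financed. Its costs therefore belong in the quantity being asked about. The stated source is a set of claims categories that names none of the program's own cost items, and several of these (network management, the IT platform, the coordination office) are by nature overhead and not care claimed for an individual patient.

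Two features make this more than a labelling issue. First, only the intervention group incurs these costs. Matching and covariate adjustment cannot remove the effect of leaving some out. Second, the article says the internet therapy may replace psychotherapeutic or psychiatric care as well as add to it. Where an uncounted module replaces a counted claim, a shift of cost appears as a saving.

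At stake is the main conclusion. An outcome that counts avoided costs but only part of the cost of avoiding them could show a reduction when net SHI spending is unchanged or higher. Strengths and Limitations does not mention this.

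**Working it through.** **Step 1: set the cost items against the data source.**

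| Program item (Intervention section) | Place in the five claims categories |
|---|---|
| Group therapy by network providers | Possibly outpatient treatment, if billed; not stated |
| Special consultation and coordination by the managing physician or therapist | Possibly outpatient treatment, if billed; not stated |
| Case management by the coordination office | None identifiable; it is called outpatient, but how it is paid is not stated |
| Internet course access | None identifiable |
| Regional network managers | None identifiable |
| IVPnet | None identifiable |
| Coordination office, general running | None identifiable |

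Two further places bear on this. The analysis section on ambulatory claims and drug prescription data identifies NPPV patients through providers who have billed NPPV services, so some program services do generate claims. Those data come from the regional physicians' association. The article does not say whether the same items reach the insurers' data. Table 2 takes use of the intervention modules from the patient survey, and Data Analyses (Overview) rules out linking survey and routine data. Survey-reported module use therefore cannot supply the cost in the primary analysis.

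**Step 2: reproduce the plan's figure.** Inputs from Sample Size Calculation: reduction 10%, coefficient of variation 0.96, power 80%, α 0.05 (taken as two-sided).

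n per group = 2 × (1.960 + 0.842)² × 0.96² / 0.10² ≈ 1447

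The article states 1456, so the figure reproduces to within 1% (one-sided would give 1140). Power at 1456 per group is 80.3%. The sample size is not in error.

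**Step 3: effect of an uncounted cost.** Let c be the uncounted program cost per participant as a share of mean control expenditure. The article gives no value, so c = 1% to 10% is an assumption.

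- Net saving = claims-based saving − c.
- Standard error at 1456 per group = 0.96 × √(2/1456) = 0.0356.
- Power for a net saving d = Φ(d/0.0356 − 1.960).
- If the true net effect is zero, the claims-based saving equals c, and the chance of declaring a saving = Φ(c/0.0356 − 1.960).

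| c | Net saving if claims show 10% | Power for the net saving | n per group for 80% power | Chance of declaring a saving if the true net effect is zero |
|---|---|---|---|---|
| 0 | 10% | 80.3% | 1447 | 2.5% |
| 1% | 9% | 71.6% | 1787 | 4.7% |
| 2% | 8% | 61.4% | 2261 | 8.1% |
| 3% | 7% | 50.3% | 2953 | 13.2% |
| 5% | 5% | 29.0% | 5787 | 29.0% |
| 10% | 0 | – | – | 80.3% |

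The break-even point is c = 10%. The table assumes that the program cost does not change the standard deviation, and it ignores clustering and matching. A larger analysed sample would not reduce the bias; it would raise the chances in the last column for any c above zero.

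**The case against.** The strongest reply is that the list in SHI Routine Data describes a data delivery and does not define cost components. The same delivery serves the other routine-data outcomes, including days of incapacity for work. The outcome is named as overall expenditure, and no sentence excludes NPPV remuneration. Some NPPV services are billed, group therapy is given by network providers, and case management is called outpatient, so part of the cost may already be counted. The clause on SHI financing can be read as applying to the program itself or to the Fund. Costing detail may also stand in the full evaluation plan, and how to allocate overhead per head is a choice of perspective.

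Most of this stands, and it limits the point. A reader might infer that the primary outcome leaves out the program's costs altogether, so that the bias equals whatever the program costs. The article does not support that: it never states an exclusion, and the billed services point the other way for at least part of the cost.

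It does not dispose of the point. On either reading of the financing clause the money is SHI money. The article itself fixes a single source for the primary outcome and describes that source in terms that give several named program items no place. That goes beyond detail left to a fuller document.

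**Conclusion.** The point holds in a limited form. As described, the data source for the primary outcome has no identifiable place for several SHI-financed program costs: the coordination office and its case management, network managers, IVPnet and internet course access. The bias is the uncounted part only. It may be small, or zero if the sponsor did add these costs. Its size cannot be computed from the article, and the percentages for c are assumptions. Two statements need no assumption about program cost: any uncounted part favours the intervention, and an uncounted cost of 10% of mean expenditure would cancel the planned saving. The stated sample size is sound and is not affected by this finding.

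**What to change.** State which NPPV costs are included in the primary outcome: provider remuneration, modules (group sessions, internet course codes, case management) and overhead (coordination office, network management, IVPnet).

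For any that are not included, do one of the following:

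- Keep the claims-based comparison as the primary result and report beside it a net SHI expenditure comparison with the missing costs added per participant. Billed services and modules go into the main net figure; a per-capita share of overhead goes into a sensitivity analysis. If costs are available only as averages, adding the average to the intervention group's mean is enough for the net difference.
- Limit the conclusion to SHI claims expenditure excluding program costs, and list this among the limitations.

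The article says data analysis is complete, so the net comparison belongs beside the primary result and should not replace it. The cost is obtaining program cost data, whose availability the article does not state, and some added wording. The estimated saving may become less favourable. The second option needs wording only.

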#### Analyses in SHI Routine Data

SHI routine data are used to evaluate the primary outcome and the secondary outcomes 1-5 (see Table 2). For all outcomes, NPPV participants are compared to a control group that is matched by propensity score matching [30]. Propensity scores are calculated using the data of the first pool of control patients and the participants in a multiple regression model estimating probability of participation in the NPPV program by personal (eg, age and gender) and health characteristics in the 12 months before inclusion date (eg, hospitalizations and frequency of out-patient treatments). The control group consists of matched persons of the second pool of control patients using the estimated propensity scores. To evaluate the outcomes, multiple regression models are estimated, controlling for relevant confounders. If necessary (high intraclass correlation coefficient), multilevel models are used to account for the hierarchical data structure (patients nested in outpatient health care providers that participate in NPPV).

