#### Patient Survey Data

For the analyses of the secondary outcomes 6-8, the data of the longitudinal survey of participants and a control group are used. The control group is drawn by direct matching with the following matching variables: inclusion diagnosis from a health care provider that is not participating in the NPPV program, 10 years age groups, gender, no resident in a care facility, no legal guardian, and grouped number of inhabitants of place of residence. To evaluate the outcomes, descriptive statistics and regression analyses are conducted using longitudinal multilevel modeling techniques.

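### In the SHI routine-data comparison, patients in other special treatment contracts are excluded from the control pools but, as written, not from the participants, so any co-enrolment would be confounded with NPPV

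*Protocol article*

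**What the plan says.** **Controls.** The section SHI Routine Data defines two pools. The first, used to estimate the propensity score, requires an inclusion diagnosis from a participating provider, adult age, and "no participation in other special treatment contracts regarding the inclusion diagnoses". The second supplies the matched controls and inherits the rule: "The second pool consists of patients with the same selection criteria as the first pool, except that these patients should not be treated by" a provider in the NPPV network.

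**Participants.** Study Population and Recruitment names "age≥18 years, insurance in one of the participating health insurance companies", and "1 or more medical condition of 7 indication groups as outlined in Table 1". Written consent is also needed. The additional criteria in Table 1 concern only diagnosis and severity. For the routine-data analysis, the one further restriction on participants is the start date: data are delivered "on each participant that started participation at least in March 2020 and control patients".

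**Adjustment.** Under Analyses in SHI Routine Data, the probability of participation is modelled "by personal (eg, age and gender) and health characteristics in the 12 months before inclusion date". The outcome regressions then control for relevant confounders. Contract participation is not named in either step.

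**The concern.** The two sides of the primary comparison have different eligibility rules. Someone in another contract for, say, depression can be analysed as a participant if enrolled in NPPV, but could not serve as a control if not enrolled. If such participants exist, the contrast becomes NPPV with or without another contract against neither.

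The primary outcome is total SHI expenditure over 12 months. A second contract could raise recorded costs (more contacts, more prescriptions) or lower them (fewer admissions). The resulting error could therefore hide a saving or mimic one, and it would not shrink with a larger sample.

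**Working it through.** **1. Can the planned adjustment remove it?** The propensity model is fitted to participants plus the first pool, and controls are drawn from the second. Nobody in either pool is in another contract. If a contract indicator were added to the model, everyone carrying it would be a participant, so no matched control could carry it. In the outcome regression the indicator would be zero for every control, so there would be no control information on what the other contract does. Matching on the prior 12 months (hospitalizations, outpatient frequency) can balance the part of the selection that shows in past utilization. It cannot remove an effect of the other contract that continues during follow-up.

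**2. The plan's own figure.** Inputs from Sample Size Calculation: 10% reduction, coefficient of variation 0.96, 80% power, α = 0.05 (taken as two-sided). In units of the control mean:

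n per group = 2 × (0.96 / 0.10)² × (1.960 + 0.842)² ≈ 1447.

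The article states 1456, so the figure reproduces closely. Power at 1456 is 80.3%. The standard error of the difference at that size is 0.96 × √(2/1456) = 0.0356, or 3.56 points.

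**3. Size of the bias.** Let q be the share of analysed participants in another contract, and d the cost difference left after matching and adjustment, relative to the control mean. The participants' mean moves by q × d. Neither value is in the article; all values below are assumptions. The rejection rate uses the two-sided 5% test with no true NPPV effect; power is for a true 10% reduction. Both are at 1456 per group.

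| q | bias (points) for d = ±10% to ±30% | rejection rate, no true effect, d = ±30% | power, d = +30% | power, d = −30% |
|---|---|---|---|---|
| 2% | ±0.2 to ±0.6 | 5.3% | 75.2% | 84.6% |
| 5% | ±0.5 to ±1.5 | 7.1% | 66.6% | 89.8% |
| 10% | ±1 to ±3 | 13.5% | 50.3% | 95.5% |
| 20% | ±2 to ±6 | 39.2% | 20.2% | 99.4% |

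Example: q = 10%, d = +30% gives 0.10 × 0.30 = 0.03. A true reduction of 10% then appears as 7%. With no true effect, the shift is 0.03 / 0.0356 = 0.84 standard errors, which gives the 13.5%.

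The gain in power for negative d is not a benefit: a true 10% saving would then be reported as larger than it is (13% at q = 10%, d = −30%).

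**4. After the change.** With the same exclusion on both sides, q = 0 and this bias is 0. The required sample size does not depend on it.

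**The case against.** **The exclusion has a purpose.** Study Design and Research Questions defines the comparator as regular care, and removing controls in special contracts implements that. The design is also called pragmatic, which can justify taking participants as they come. This explains the rule for controls, but it does not make the two groups comparable when the rule is one-sided.

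**Co-enrolment is not shown.** The article does not say that any participant is in another contract, or whether dual enrolment is possible at all. A fuller protocol or the participation terms may rule it out. This stands, and it makes the point conditional. A reader might infer that effects and costs of other contracts are in fact being counted as NPPV effects. The article does not support that: co-enrolment is unreported, and payments under such contracts are not named among the data the insurers deliver. Only effects on the recorded costs and utilization are at issue.

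**The sizes are assumed, and matching absorbs some of the difference.** Both are right. That is why d is defined as what remains after matching, and why small shares are shown. At q = 2% the matter is minor.

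**The survey.** A reader might extend the point to the patient survey, where "The control group is drawn by direct matching with the following matching variables" and no contract rule is listed. That does not follow. No such exclusion is stated for either survey group, so the two sides are treated alike. The survey is not linked to the routine data and serves other outcomes (6 to 8).

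**Conclusion.** The point holds in conditional form and only for the SHI routine-data comparison. As printed, eligibility is asymmetric on other special treatment contracts, and the planned matching and regression cannot correct for it. If participants are co-enrolled, the remaining effect of the other contract on recorded costs and utilization is confounded with NPPV.

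Under assumed values, the bias is negligible to small at q = 2% (at most 0.6 points for d up to 30%) and reaches 3 points, about a third of the planned 10% reduction, at q = 10% with d = 30%. The direction is unknown, so it cannot be called conservative. If the full protocol already bars or removes co-enrolled participants, the bias is absent and one clarifying sentence is enough.

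**What to change.** In SHI Routine Data and Analyses in SHI Routine Data, state that participants in another special treatment contract for an inclusion diagnosis at their inclusion date are left out of the main routine-data analysis (primary outcome and secondary outcomes 1 to 5), matching the rule for the control pools. Report how many participants this removes, and present the result for all participants as a sensitivity analysis. Admission to the programme does not change, and neither does the survey matching. Since the article reports that data analysis is complete, this can be done as a restricted re-analysis, or as a clarification if the rule was in fact applied.

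**Cost.** The insurers already need to identify these contracts to build the control pools. The analysed group shrinks by the share q, and the main result no longer covers patients in two contracts. Precision is unlikely to suffer. Keeping 1456 participants needs 1456 / 0.90 ≈ 1618 before exclusion at q = 10%, or 1456 / 0.80 = 1820 at q = 20%. Up to 14,000 are planned in total, although the number who started early enough for this analysis is not stated.
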